### **The intervention**

The intervention is to provide AI-based dish nutrition evaluation and PN evaluation after meal consumption at the study canteen through the applet (Figure 2). The applet based on privacy-preserving computing platform has two interfaces: a phone-based client and a web-based data management system. For users, this applet is a WeChat mini-program which has ease of use, high acceptance and little memory. Similar to Facebook, WeChat is a very popular social software in China. The mini-program relying on WeChat can achieve health functions and provide native app-like experiences without leaving WeChat interface. For researchers, the web-based system is used to facilitate central management including user registration, recipe preparation, menu administration and information storage. The built-in AI algorithm is applied in data operation and processing to support iterative calculation.

Figure 2. User interfaces of the AI-based PN management applet.

[figure not shown]

Screen 1

[figure not shown]

Screen 2

Note: Screen 1 demonstrates dish nutrition evaluation. Screen 2 shows PN evaluation after meal consumption.

### ***Dish nutrition evaluation***

Dish nutrition evaluation is used to determine whether the content of fat, sodium and sugar in dish is benefit for health.

Two independent datasets are used for our study. First is the Chinese food composition database , which is publicly available. This database includes nutritional values for over 1110 food items and corresponding food groups. Second, we create a recipe dataset of all the dishes supplied in this canteen. The recipe includes the raw weights of materials (including ingredients and condiments) and their edible proportion, as well as gross and single-portion cooked weights of each

dish. Weight measurements are conducted by field investigators with expertise in nutrition under the same standard criteria.

We construct a full dish/nutrition dataset by connecting the recipe dataset to Chinese food composition database. Thus, the food groups, energy and nutrients for each dish are automatically calculated using Algorithm 1. Food groups are classified as cereals & tubers (grains, potatoes and tubers), vegetables (excluding legumes), fruits (including citrus), livestock and poultry meat, eggs and products, seafood, dairy, nuts, soybeans and products, cooking oil, salt and sugar. Plant food stands for cereals & tubers, vegetables, fruits, soybeans and products. Animal food stands for livestock and poultry meat, seafood, eggs and products. Nutrients include protein, fat, carbohydrate, cholesterol, sodium, calcium, iron, zinc and vitamin C.

Algorithm 1. Calculation of food groups, energy and nutrients for each dish

$$dish = (food\ item[1], food\ item[2], \dots, food\ item[m])^1$$

$$Weight_{food\ group, dish} = \sum_{i \in dish} Raw\ Weight[i] \times Edible\ Proportion[i] \times \frac{Cooked\ Weight_{single-portion\ dish}}{Cooked\ Weight_{gross\ dish}}^2$$

$$Energy_{dish} = \sum_{i \in dish} Raw\ Weight[i] \times Edible\ Proportion[i] \times \frac{Energy[i]}{100} \times \frac{Cooked\ Weight_{single-portion\ dish}}{Cooked\ Weight_{gross\ dish}}^3$$

$$Nutrient_{dish} = \sum_{i \in dish} Raw\ Weight[i] \times Edible\ Proportion[i] \times \frac{Nutrient[i]}{100} \times \frac{Cooked\ Weight_{single-portion\ dish}}{Cooked\ Weight_{gross\ dish}}^4$$

 By matching two datasets, food item represents raw material (ingredient or condiment) in dish.

 Similar food items are merged into predetermined food groups.

 According to Chinese food composition database, energy[j] refers to content of energy in 100g edible portion of food item[j].

 According to Chinese food composition database, nutrient[j] refers to content of nutrient in 100g edible portion of food item[j].

The intervenors can browse and choose dishes on the ordering interface of the applet. Colored dots are displayed next to the dishes' names by a "traffic light" approach to indicate whether the dishes are benefit for health. The judgement of three colors is based on the contents of fat, sodium and sugar (green = reaching the dietary

recommendations, yellow = between the recommendations and average intakes among Chinese population , red = above the upper limit of intakes). The dietary recommendations in this study are: no more than 8g fat, 500mg sodium and 4.5g sugar in 100g dish (raw weight except for condiments). The cutoffs of nutrient contents according to the definition of “traffic lights” are listed in Table 2.

Table 2. The cutoffs of nutrient contents for dish nutrition evaluation

| Nutrient content               | I    | II       | III   |
|--------------------------------|------|----------|-------|
| Fat (g/100g  )     | <8   | 8-20     | >20   |
| Sodium (mg/100g  ) | <500 | 500-1000 | >1000 |
| Sugar (g/100g  )   | <4.5 | 4.5-9    | >9    |

 Green light for the dish represents all three indices within the range in the I column, red indicates at least 1 index within the range in the III column and yellow includes all the others.

 100g refers to 100g edible portion of dish.

### ***PN evaluation after meal consumption***

PN evaluation after meal consumption is used to illustrate whether food intakes are inadequate, adequate or excessive.

A meal may consist of different dishes in varying portions. To obtain the actual intake of each chosen dish, nutritional values are multiplied by portions and non-discarded proportion that are input by participants on the ordering interface. Subsequently, to calculate the meal consumption, the consumptions of corresponding food groups, energy and nutrients from different dishes are summed up (Algorithm 2). The whole-day consumption can be further calculated according to self-reported contribution of three meals to total daily food intake.

Algorithm 2. Calculation of food groups, energy and nutrients for meal

$$meal = (dish[1], dish[2], \dots, dish[n])$$

$$Weight_{food\ group, meal} = \sum_{j \in meal} Weight_{food\ group, dish[j]} \times Portions[j] \times (1 - discarded\ proportion[j])$$

$$Energy_{meal} = \sum_{j \in meal} Energy_{dish[j]} \times Portions[j] \times (1 - discarded\ proportion[j])$$

$$Nutrient_{meal} = \sum_{j \in meal} Nutrient_{dish[j]} \times Portions[j] \times (1 - discarded\ proportion[j])$$

According to individual's biological profile and total energy expenditure (TEE), the specific recommended intake of the individual will be determined. TEE can be calculated using resting energy expenditure (REE) multiplied by PAL. REE is estimated by Schofield equation regarding age, sex and body weight. PAL is categorized into 1.5 for light, 1.75 for moderate, and 2.0 for vigorous physical activity. Based on Chinese Food Recommendation, TEE ranging from 1000 kcal/day to 3000 kcal/day can be divided to 11 ranks and nutrition needs for a balanced diet pattern vary with different TEE ranks. Taking self-reported contribution of three meals to total daily food intake into consideration, recommendations of food groups and nutrients per meal can be assessed according to Chinese Dietary Guidelines and Chinese Dietary Reference Intakes (DRIs), respectively.

By comparison with recommended intake, the PN evaluation regarding actual intake will be provided for participants. The key evaluation indices for meal consumption are described in Table 3, including fat, sodium, meat and vegetables. For each index, we assign a health score with a corresponding mark to illustrate the comparisons between the current consumption and the national dietary recommendations. For example, a mark of three plus (+++) for fat indicates that the percentage of energy intake from fat is far from recommendation. Evaluation of fat and sodium is given greater weight than others, with a score of 0-3, because these two dietary factors are more related to burden of NCDs in China. Finally, an aggregate score of all the indices will be obtained, which represents the healthiness of whole meal consumption, 0 being the unhealthiest, and 10 being very healthy.

Table 3. The key evaluation indices for meal consumption

| Evaluation index                                    | Range  | Health score | Mark |
|-----------------------------------------------------|--------|--------------|------|
| Fat: percentage of energy intake from fat, % | <20    | 2            | —    |
|                                                     | 20-<30 | 3            | Good |
|                                                     | 30-<40 | 2            | +    |
|                                                     | 40-<50 | 1            | ++   |
|                                                     | 50-<60 | 0.5          | +++  |

|                                                    |            |     |      |
|----------------------------------------------------|------------|-----|------|
|                                                    | >60        | 0   | ++++ |
| Sodium: actual intake, mg                   | <1000      | 3   | Good |
|                                                    | 1000-<1400 | 2   | +    |
|                                                    | 1400-<1800 | 1   | ++   |
|                                                    | 1800-<2200 | 0.5 | +++  |
|                                                    | >2200      | 0   | ++++ |
| Meat: actual/recommended intake ratio       | <0.8       | 1   | —    |
|                                                    | 0.8-<1.2   | 2   | Good |
|                                                    | 1.2-<1.4   | 1   | +    |
|                                                    | >1.4       | 0   | ++   |
| Vegetables: actual/recommended intake ratio | <0.5       | 0   | — —  |
|                                                    | 0.5-<0.7   | 1   | —    |
|                                                    | >0.7       | 2   | Good |

---

217

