## Methods

### Setting and study design

This trial is a two-arm parallel, randomized, controlled study in real-world situations. This smartphone applet with built-in AI-based algorithm only takes effect where dishes prepared by recipes with quantity (in China, same dish prepared at different home are different in cooking but dishes in central kitchen or food factory are prepared strictly following standard cooking procedure ). Participants are enrolled sequentially until the sample size reaches requirement. This study will be carried out in a pilot company employing 3000 people and food is prepared by the central kitchen at staff canteen. All participants will choose and consume meals on their own wills during the study. Weight and blood pressure measuring tools placed at the canteen can be available to participants; therefore, they can conveniently measure and record anthropometric indicators through the applet.

**Phase I.** The employees will be recruited to dine in the canteen for 3 months, assigned to the intervention or control group randomly. Both groups will be asked to use the applet to record their lunch each weekday during the study. After 1 week of run-in period, the intervention group will be able to access the information of dish nutrition evaluation and PN evaluation after meal consumption, while the control group will not. Both groups will be followed up by researchers on the same time schedules for the outcome measurements.

**Phase II.** Full-functioned applet will be available for use by all the diners (about 800) for another 1 year. Who use the applet at least 2 days per week will be regarded as the intervention group while the others will be the control group. During this phase, metabolic indicators from the annual physical examination will be provided by the company.

Figure 1 outlines the study design and Table 1 presents the visits and data

60 collection schedule.

61

62 Figure 1. Study design of the trial.

[figure not shown]

63

64

65 Table 1. Visits and data collection schedule

|                           | Phase I (3 months) |        |           | Phase II (1 year) |        |           |
|---------------------------|--------------------|--------|-----------|-------------------|--------|-----------|
|                           | Screening          | Run-in | Follow-up | Screening         | Run-in | Follow-up |

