## 67 Sample size

68 In Phase I, the planned sample size per group was determined as 70 to detect an  
 69 assumed intervention effect size of 0.25 in animal/plant food ratio over 4 months.  
 70 Statistical power was set at 90% with a significance level of 5%, using an SD in  
 71 animal/plant food ratio of 0.41 from the Shanghai Diet and Health Survey ,  
 72 considering a 15% dropout rate. In Phase II, assuming that the prevalence of

metabolic syndrome after intervention is approximately 20% based on the available research evidence, we would need 200 participants in each group to have sufficient power to detect the given effect size.

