## 218 **Outcomes**

219 In Phase I, dietary pattern, body weight or blood pressure optimizing is expected  
220 after the intervention. The primary outcome for the intervention effectiveness is  
221 dietary intakes. Anthropometric indicators including weight, body mass index (BMI),  
222 body composition and blood pressure are the secondary outcome. In Phase II, body  
223 metabolism normalization is expected after this period.

224

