## 233 **Statistical analysis**

234 The Mann-Kendall test will be implemented to examine the temporal trends of  
235 lunchtime food supply based on average “traffic light” score and animal/plant food  
236 ratio. For dietary record, we hypothesized that at least 5000 person-meal observations  
237 would be collected and analyzed over the follow-up period. Generalized linear mixed

models with intervention, time and 2-way interaction as fixed factors, will be used to examine the intervention effects on each outcome. A two-sided  $p$  value  $< 0.05$  will be considered to indicate statistical significance.

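### In Phase I the dietary outcome rests on portions and discards typed in by participants, and the same entries drive a score that only the intervention arm sees, so one-arm mis-entry could look like a dietary effect

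*Protocol*

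**What the plan says.** All references are to the Protocol.

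- **Source of the data.** Both arms log weekday lunches in the applet (Setting and study design). Under PN evaluation after meal consumption, "nutritional values are multiplied by portions and non-discarded proportion that are input by participants on the ordering interface". Algorithm 2 applies that multiplier to food-group weights, energy and nutrients alike.
- **Outcome.** "The primary outcome for the intervention effectiveness is" dietary intakes (Outcomes). No index or scale is named. The only dietary measure with a planning figure is the animal/plant food ratio, with an "assumed intervention effect size of 0.25 in animal/plant food ratio over 4 months" (Sample size).
- **Who sees the evaluation.** After the one-week run-in, the intervention arm gets the dish evaluation and the "PN evaluation after meal consumption, while the control group will not" (Setting and study design).
- **What the score rewards.** Table 3 scores sodium on "actual intake, mg", fat as a share of energy, and meat and vegetables as ratios of actual to recommended intake.
- **Analysis.** Mixed models with intervention, time and their interaction will "examine the intervention effects on each outcome" (Statistical analysis).
- **Checks.** Quality control provides for on-site and on-line data review. It states no weighing or independent check of portions or leftovers.

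**The concern.** Ordinary self-report error affects both arms alike and mainly adds noise. Here the protocol links the error to allocation: one set of typed entries is both the outcome and the input to a score that one arm sees and can improve. A participant can raise that score by eating differently or by typing differently, and the record does not separate the two.

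The pull begins after randomisation and acts in one arm, so neither randomisation nor a larger number of recorded meals removes it. The intervention-by-time interaction would absorb it as part of the effect. At stake is whether a significant fall in sodium, meat or the animal/plant ratio can be read as a change in eating.

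**Working it through.** **1. The plan's own figure.** Inputs from Sample size: difference 0.25, SD 0.41, power 90%, dropout 15%; the 5% level is two-sided (Statistical analysis).
n per group = 2 × (1.960 + 1.282)² × 0.41² / 0.25² = 56.5, rounded up to 57. Then 57 / 0.85 = 67.1, rounded up to 68. The stated 70 is consistent with this. Completers per arm: 70 × 0.85 = 59.5.

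**2. What uniform under-entry does.** If every entry is multiplied by f, Algorithm 2 lowers each absolute intake by 1 − f; at f = 0.8, sodium, meat, vegetables and energy all fall by 20%. Fat as % of energy and the animal/plant ratio do not change, because f cancels.

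**3. Which way the score pulls.** Sodium + meat + vegetable points from Table 3, with the fat index left out because uniform scaling does not move it:

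| Lunch (sodium mg; meat ratio; vegetable ratio) | Entered in full | All entries × 0.8 |
|---|---|---|
| 1500; 1.3; 0.9 | 1 + 1 + 2 = 4 | 2 + 2 + 2 = 6 |
| 1500; 1.0; 0.6 | 1 + 2 + 1 = 4 | 2 + 2 + 0 = 4 |
| 900; 0.9; 0.6 | 3 + 2 + 1 = 6 | 3 + 1 + 0 = 4 |

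On an assumed flat grid (sodium 800 to 2600 mg, meat 0.6 to 2.0, vegetables 0.4 to 1.4), 20% uniform under-entry raises the three-index score in 61% of cells, leaves it in 18% and lowers it in 21%. At 10% the shares are 46%, 38% and 16%. There is a net pull towards smaller entries, but not a consistent one.

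Selective entry pays more reliably. Take 1500 mg, meat 1.3, vegetables 0.6, which scores 1 + 1 + 1 = 3. Enter meat dishes at 0.8 (ratio 1.04, 2 points) and vegetable dishes at 1.2 (ratio 0.72, 2 points). Entered sodium then lies between 1200 mg (all from the meat dishes, 2 points) and 1800 mg (all from the vegetable dishes, 0.5 points). The total is 4.5 to 6, with no change in eating.

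**4. Effect on the animal/plant ratio.** The baseline ratio is not given; 0.4 to 1.0 is assumed. Under-entry of animal food by a share u in one arm shifts the ratio by baseline × u. With a simple comparison of person means, SE = 0.41 × √(2 / 59.5) = 0.075, and the rejection probability is Φ(shift/SE − 1.96) + Φ(−shift/SE − 1.96).

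| u (assumed) | Shift | False-positive probability |
|---|---|---|
| 10% | 0.04 to 0.10 | 8% to 26% |
| 20% | 0.08 to 0.20 | 19% to 76% |

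A spurious shift equal to the full 0.25 needs u = 0.25 / 0.4 = 62.5% down to 0.25 / 1.0 = 25%. Portions are entered per dish, so under-entering a mixed dish also lowers its plant content and the shift is then smaller.

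**5. Effect on absolute sodium.** Assumed: mean lunch sodium 1200 to 1800 mg, SD of person means 400 to 500 mg, 60 per arm, uniform under-entry in one arm. SE = SD × √(2 / 60) = 73 to 91 mg. Under-entry of 5% gives 60 to 90 mg and a false-positive probability of 10% to 23%; 10% gives 120 to 180 mg and 26% to 69%.

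**6. What energy adjustment can and cannot do.** Sodium per 1000 kcal is unaffected by uniform under-entry, by construction. It does not cure selective entry. If animal dishes are under-entered by 10% and supply 30% to 50% of lunch energy (assumed), meat per 1000 kcal becomes 0.90 / 0.97 = 0.93 to 0.90 / 0.95 = 0.95 of its true value, still 5% to 7% low.

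**The case against.** The strongest reply is that the protocol never commits to absolute intakes. Its only sized dietary measure is a ratio and its fat index is a share of energy, and uniform under-entry moves neither. Energy adjustment and sensitivity analyses are commonly left to the SAP, which is not shown. A reader might infer that Phase I compares absolute lunch intakes without energy adjustment; the text does not say so. This part stands. It does not dispose of the point, because selective mis-entry moves the ratio too, and the double use of the entries is fixed in the protocol itself.

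A reader might also infer that the score simply rewards smaller entries. Table 3 does not support that: vegetables gain from larger entries, meat below 0.8 loses a point, and fat as % of energy ignores uniform scaling. Large gains can be constructed: 1400 mg, meat 1.45 and vegetables 1.1 goes from 3 to 7 points. But that takes 30% under-entry from values at the band edges. The same lunch gains 2 points at 5% or 10%, and one with 1390 mg, 1.1 and 0.75 loses a point at 10%.

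Third, eating less of a food in excess is an intended effect of the evaluation. Making energy-adjusted values the main comparison, or barring a claim about absolute intake unless they agree, would discard a genuine portion reduction. This stands, and the fix is limited accordingly.

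**Conclusion.** The point holds as a route to bias, not as a measured bias. The documents establish that participants' own entries scale every recorded intake, that those entries feed a score visible in one arm only, and that no check of portions or waste is described. The likely distortion is selective: less meat and salty food entered, more vegetables. It can reach both absolute intakes and the animal/plant ratio.

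Its size cannot be computed from the documents. The under-entry rates, lunch sodium mean and SD, and baseline ratio are all assumptions. The false-positive probabilities show that modest mis-entry would matter at this sample size; they do not say that it will occur. Nor do the documents support the inference that switching to energy-adjusted outcomes would settle the matter. The planned sample size is not in question. This is a cheap safeguard on interpretation.

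**What to change.** In Statistical analysis, for the Phase I dietary outcomes:

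1. Prespecify a sensitivity analysis that recomputes each dietary outcome, including the animal/plant ratio, with Portions = 1 and discarded proportion = 0 for every chosen dish in both arms, so that only dish choice counts.
2. Report the between-arm difference in change from run-in in entered portions and in discarded proportion.
3. Report sodium and food groups per 1000 kcal of the recorded lunch, and fat as % of energy, alongside the absolute values and not in place of them.
4. State that an effect appearing only through the portion and discard entries may reflect reporting and not eating.

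**Cost.** Protocol wording and a few extra model runs on entries that the applet already takes from both arms.

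**Limits.** The dish-choice analysis gives no credit for a genuine portion reduction and does not detect omitted dishes. The comparison of entries cannot by itself separate eating less from typing less. Both therefore support the main analysis and do not replace it.

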## 218 **Outcomes**

219 In Phase I, dietary pattern, body weight or blood pressure optimizing is expected  
220 after the intervention. The primary outcome for the intervention effectiveness is  
221 dietary intakes. Anthropometric indicators including weight, body mass index (BMI),  
222 body composition and blood pressure are the secondary outcome. In Phase II, body  
223 metabolism normalization is expected after this period.

224

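### The Phase I primary outcome is dietary intakes in the plural, but the 5% significance and 90% power were set for one variable, the animal/plant food ratio, which is never named as primary

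*Protocol*

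**What the plan says.** Three sections of the protocol bear on this.

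- **Outcomes.** For Phase I: "The primary outcome for the intervention effectiveness is", continued on the next line by "dietary intakes. Anthropometric indicators including weight, body mass index (BMI". The primary outcome is thus a plural category. No variable, summary measure or time point is singled out, and the animal/plant food ratio is not mentioned.
- **Sample size.** "In Phase I, the planned sample size per group was determined as 70 to detect an" "assumed intervention effect size of 0.25 in animal/plant food ratio over 4 months". The error rates follow: "Statistical power was set at 90% with a significance level of 5%, using an SD in" "animal/plant food ratio of 0.41 from the Shanghai Diet and Health Survey", "considering a 15% dropout rate". Only this one variable is used.
- **Statistical analysis.** Mixed "models with intervention, time and 2-way interaction as fixed factors, will be used to examine the intervention effects on each outcome", with a single two-sided threshold of 0.05. The animal/plant ratio appears in this section only for the Mann-Kendall trend in what the canteen supplies, not for what participants eat.

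Two other sections show how much the words dietary intakes could cover. Dish nutrition evaluation lists 12 food groups, energy and 9 nutrients, and it defines plant and animal food. PN evaluation after meal consumption gives a shorter list of four key indices (fat, sodium, meat, vegetables) and an aggregate score.

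**The concern.** A sample size calculation ties its significance level and power to one test of one variable. Here that variable is not declared primary, and the category that is declared primary holds several variables, each to be tested at the same unadjusted level. A reader of the final report could not tell from the protocol which result decides the trial. A null result for the ratio beside a p value of 0.04 for some other food group or nutrient would be compatible with claiming an effect on the primary outcome. The stated 90% power, in turn, belongs to no declared primary outcome. What is at stake is the trial's main claim.

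**Working it through.** **1. Reproduce the planned size.** Inputs from the Sample size section: difference δ = 0.25, SD σ = 0.41, two-sided α = 0.05, power 90%, dropout 15%. Allocation is 1:1 (Randomization and blinding).

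n per group = 2 (z₀.₉₇₅ + z₀.₉₀)² σ² / δ² = 2 × (1.960 + 1.282)² × 0.1681 / 0.0625 ≈ 56.5, so 57.

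With dropout: 57 / 0.85 = 67.1, so 68. The t-test version gives 58, and 58 / 0.85 = 68.2, so 69. Both agree with the stated 70. Of the alternatives tried, one-sided 5% at 90% power gives 56 after dropout and two-sided 5% at 80% power gives 51; neither reproduces it. The 70 per group is therefore the size for **one** two-sided 5% test of the ratio. With 70 × 0.85 = 59.5, say 59 completers per group, power for that test is 91%. The arithmetic is sound. (The 4-month horizon in the sizing sentence against a 3-month Phase I is a separate matter and does not enter this formula.)

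**2. Error rate when several intakes are primary.** For k independent tests at 0.05 with no true effect, the chance of at least one significant result is 1 − 0.95^k. For correlated tests, equicorrelated normal test statistics were simulated (200,000 replicates). Both k and the correlation ρ are assumptions, because the protocol gives neither.

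| k | ρ = 0.8 | ρ = 0.5 | ρ = 0.3 | independent |
|---|---|---|---|---|
| 2 | – | – | – | 9.75% |
| 4 | 11% | 16% | 17% | 18.5% |
| 12 | 18% | 32% | 40% | 46.0% |
| 23 | 24% | 45% | 58% | 69.3% |

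Here 4 is the number of key meal indices, 12 the number of food groups, and 23 = 12 food groups + 1 energy + 9 nutrients + 1 ratio. Every case computed lies above 5%.

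**3. What each way out would cost.** If the ratio is the sole primary outcome, step 1 applies unchanged and 70 per group stands. If several intakes were kept as primary with a Bonferroni split α = 0.05/k, then, assuming the same δ and σ for each:

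| k | n per group | after 15% dropout | power for the ratio with 59 completers |
|---|---|---|---|
| 1 | 57 | 68 | 91% |
| 2 | 67 | 79 | 86% |
| 4 | 77 | 91 | 79% |
| 12 | 93 | 110 | 67% |
| 23 | 102 | 120 | 60% |

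**The case against.** The strongest reply is that this is loose wording, not a contradiction. The ratio is itself a measure of dietary intake, the protocol defines its two components, and Phase I is sized on it, so a reader could take it as the intended lead variable. Multiplicity procedures and test ordering are commonly left to the statistical analysis plan, which is not at hand. Part of this stands: the absence of a multiplicity procedure is not counted here. But which variable is primary, and its link to the sample size, are matters for the protocol, and the protocol has fixed them in sections that do not match.

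Three stronger readings are tempting and are not supported.

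- *The trial has 23 primary tests and a 69% false-positive risk.* The 23 quantities come from the description of the applet's dish calculations, which is not an outcome list. They also overlap (salt with sodium, oil with fat, energy with macronutrients, the ratio with its components), so independence is the extreme case.
- *The 5% level is lost altogether.* It holds for the ratio tested alone.
- *Any significant intake will be declared a primary success.* The protocol states no success rule. The text permits this, but does not say it will happen.

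**Conclusion.** Wrong as written. The primary outcome as defined is wider than the variable on which the trial is sized, and each outcome is tested at a flat 0.05, so neither the 5% nor the 90% attaches to the declared primary outcome. The direction is certain once two or more intakes count as primary; the size is not. It runs from about 10% (2 independent tests), through 11–18% (4 tests), to 24–69% (23 tests, from correlation 0.8 to independence), against the intended 5%. These figures rest on assumed numbers of tests and assumed correlations. The sample size itself is not at fault.

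**What to change.** In Outcomes, name one primary outcome for Phase I: the participants' animal/plant food ratio from the recorded canteen lunches after the run-in week. In Statistical analysis, state that this outcome is tested by the mixed model already planned, at two-sided 5%. List all other food groups, energy, nutrients and meal indices as secondary or exploratory, and say that they cannot carry the primary claim.

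The cost is a few sentences in two sections, and 70 per group stands. The downside is that an effect seen only in other intakes can no longer support the primary claim. If the sponsor prefers several primary intakes, a multiplicity procedure and a new sample size are needed; the second table under the working shows the scale.

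How the ratio is aggregated over meals is optional for this fix. If the aggregation is changed, the SD of 0.41, which comes from an external survey, must be justified for the new form.
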